## Outcome Measures

### Primary Outcome Measure:

- Vital signs**  
 Systolic Blood Pressure (mmHg) Description: Systolic blood pressure levels measured during the perioperative period.  
 [Time Frame: Preoperative, immediately postoperative, and 8 hours postoperative.]
- Diastolic Blood Pressure (mmHg)**  
 Diastolic blood pressure levels will be measured to assess changes in blood pressure during the perioperative period.  
 [Time Frame: Preoperative, immediately postoperative, and 8 hours postoperative]
- Heart Rate (bpm)**  
 Heart rate will be measured to monitor cardiac activity during the perioperative period.  
 [Time Frame: Preoperative, immediately postoperative, and 8 hours postoperative]
- Body Temperature (°C)**  
 Body temperature will be measured to observe temperature changes during the perioperative period.

[Time Frame: Preoperative, immediately postoperative, and 8 hours postoperative]

5. Hemoglobin (g/dL)

Hemoglobin levels will be measured preoperatively and within 24 hours postoperatively to evaluate changes in blood parameters during the perioperative period.

[Time Frame: Preoperative and 24 hours postoperative]

6. Creatinine (mg/dL)

Creatinine levels will be measured preoperatively and within 24 hours postoperatively to monitor renal function during the perioperative period.

[Time Frame: Preoperative and 24 hours postoperative]

7. Glucose (mg/dL)

Glucose levels will be measured preoperatively and within 24 hours postoperatively to assess perioperative glucose regulation

[Time Frame: Preoperative and 24 hours postoperative]

Secondary Outcome Measure:

8. Secondary Outcome Measure

Pain Score: The Visual Analog Scale (VAS) was used to measure pain intensity in children during the postoperative period following tonsillectomy and adenoidectomy. The children were assessed using the Visual Analog Scale (VAS) before surgery, immediately after returning to the ward post-surgery, and 8 hours after surgery. The Visual Analog Scale (VAS) ranges from 0 to 10, with 0 indicating no pain and 10 representing the worst possible pain. Higher scores indicate greater pain intensity.

[Time Frame: Preoperative, immediately postoperative, 8 hours postoperative]

Other Pre-specified Outcome Measures:

9. Tertiary Outcome Measure

Anxiety Score: The Perioperative Multidimensional Anxiety Scale for Children is a visual analog scale consisting of 5 items, each scored between 0 and 100. The scale was used to measure anxiety levels in children during the perioperative period.

[Time Frame: Preoperative, immediately postoperative, 8 hours postoperative]

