### Study Identification

Unique Protocol ID: İzmirTınaztepeÜ-[name]-001

Brief Title: Preoperative VR Cartoon Viewing Reduces Postoperative Pain and Anxiety in Pediatric Tonsillectomy Patient

Official Title: The Effect of Preoperative Virtual Reality Cartoon Viewing on Postoperative Pain and Anxiety in Children Undergoing Tonsillectomy and Adenoidectomy

Secondary IDs:

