## Study Description

**Brief Summary:** The aim of this study is to determine the effect of watching a cartoon with a virtual reality headset before surgery on the pain and anxiety levels of children aged 7-12 years.

**Detailed Description:** The aim of this study is to determine the effect of watching a cartoon with a virtual reality headset before surgery on the pain and anxiety levels of children aged 7-12 years. In line with this aim, children aged 7-12 who were scheduled for tonsillectomy and adenoidectomy at the Ear, Nose, and Throat Department of Uşak University Education and Research Hospital were shown a cartoon with a virtual reality headset before surgery, and their pain and anxiety levels were examined. The study was conducted as a randomized controlled experimental study at the Ear, Nose, and Throat Unit of Uşak University Education and Research Hospital. The population of the study consisted of children aged 7-12 who applied for tonsillectomy and adenoidectomy surgery at the Ear, Nose, and Throat Unit of Uşak University Education and Research Hospital. The sample of the study included a total of 102 children, with 51 in the experimental group and 51 in the control group, who met the research criteria and volunteered to participate in the study between November 10, 2023, and June 1, 2024. Data collection tools included the informed consent form, sociodemographic questionnaire, vital signs assessment form, Visual Analog Scale, and the Perioperative Multidimensional Anxiety Scale for children.

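### None of the seven primary outcomes measures pain or anxiety, the trial's only stated question; pain is ranked secondary and anxiety tertiary

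*Protocol*

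**What the plan says.** Under Study Identification the official title is "The Effect of Preoperative Virtual Reality Cartoon Viewing on Postoperative Pain and Anxiety in Children Undergoing Tonsillectomy and Adenoidectomy". The brief title names the same two constructs and words them as a result: viewing the cartoon lowers both. Study Description gives a single aim, in both the brief summary and the detailed description: the "effect of watching a cartoon with a virtual reality headset before surgery on the pain and anxiety levels of children aged 7-12 years".

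Under Outcome Measures, the primary list has seven entries. The first is "Systolic Blood Pressure (mmHg) Description: Systolic blood pressure levels measured during the perioperative period". The next three are further vital signs, each with its own stated purpose: "Diastolic blood pressure levels will be measured to assess changes in blood pressure during the perioperative period", "Heart rate will be measured to monitor cardiac activity during the perioperative period" and "Body temperature will be measured to observe temperature changes during the perioperative period". The last three are hemoglobin, creatinine and glucose, measured before surgery and by 24 hours after it. Their stated purposes are blood parameters, renal function and glucose regulation.

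Pain is the only secondary outcome: "Pain Score: The Visual Analog Scale (VAS) was used to measure pain intensity in children during the postoperative period following tonsillectomy and adenoidectomy". Anxiety comes last, among the other pre-specified outcomes, and is labelled tertiary: "The scale was used to measure anxiety levels in children during the perioperative period".

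**The concern.** The primary outcome is supposed to carry the trial's main conclusion. Here the stated question and the primary list do not overlap at all. Whatever the seven primary results turn out to be, they are results about blood pressure, pulse, temperature and blood chemistry, and they say nothing direct about pain or anxiety.

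What is at stake is the standing of the claim that the brief title already makes. Under the record's own hierarchy it rests on one secondary and one tertiary outcome. A report that leads with pain and anxiety would draw its headline from non-primary outcomes. A report that silently called them primary would contradict the record.

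**Working it through.** The check is a comparison of sections; the document gives no sample-size calculation to reproduce.

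**1. Question against ranking.**

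| Outcome | Rank in record | Named in titles or aim |
|---|---|---|
| 1 Systolic pressure | Primary | No |
| 2 Diastolic pressure | Primary | No |
| 3 Heart rate | Primary | No |
| 4 Temperature | Primary | No |
| 5 Hemoglobin | Primary | No |
| 6 Creatinine | Primary | No |
| 7 Glucose | Primary | No |
| 8 Pain (VAS) | Secondary | Yes |
| 9 Anxiety | Other, labelled tertiary | Yes |

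Four vital signs plus three blood tests make 7 primary outcomes. Of these, 0 of 7 measure a construct in the aim. Both constructs in the aim (2 of 2) are non-primary, in places 8 and 9 of 9.

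**2. Are the seven offered as proxies?** The reasons given in the outcome list are physiological monitoring. No entry links its measure to pain or anxiety.

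**3. Does another section support the primary list?** It does not.
- The outcome-related keywords under Conditions are pain level and anxiety level.
- Eligibility asks that children understand pain and anxiety scales.
- The data collection tools in Study Description, and the assessments for each arm in Arms and Interventions, cover vital signs, pain and anxiety. Neither place names hemoglobin, creatinine or glucose.

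So 3 of the 7 primaries are missing from the described procedures, while both constructs in the aim are present in them.

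**4. Were pain and anxiety collected?** Yes. Arms and Interventions gives the same three assessments for both groups: before surgery, on return to the ward, and 8 hours after surgery.

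**5. Timing of any change.** Study Status gives completion on July 13, 2024, and the record was released on January 1, 2025. A re-ranking made now comes after the data.

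**6. What the seven primaries would imply for a claim of success.** The document states no success rule, so the consequence depends on an assumption. If any one of seven independent tests at an assumed two-sided 5% level were enough, the chance of at least one false positive would be 1 − 0.95^7 = 0.302; positive correlation between outcomes would lower it. If all seven had to succeed, one null result would be decisive. The finding depends on neither case.

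**The case against.** **Proxy defence.** Heart rate and blood pressure might be defended as indirect markers of distress. The document does not say so. The defence would also leave temperature, hemoglobin and creatinine unexplained, and glucose is listed only for its regulation. It does not stand.

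**The analysis plan may settle it.** A separate plan could hold a success rule or a multiplicity procedure. It would not remove the conflict between this record's aim and its primary list.

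**The aim can still be addressed.** This stands. Pain and anxiety were assessed in both arms at every time point, so the failure is in the primary analysis as ranked and not in the trial as a whole.

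**Re-ranking after completion is itself outcome selection.** This also stands, and it limits the remedy. The titles and aim give pain and anxiety equal standing, and nothing prefers one postoperative assessment over the other. The rest of the cartoon was shown one hour after surgery, and the record does not say whether the first ward assessment came before or after it. Choosing one outcome, one time point or a testing order now would be a post hoc preference and could not restore confirmatory status.

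**Stronger readings that the document does not support.**
- A reader might infer that a null creatinine or temperature result makes the trial formally negative. That needs an all-must-succeed rule, which the document does not state.
- A reader might infer that 51 children per arm suffice for pain or anxiety as a single primary, since about 0.56 SD is detectable. That figure assumes two-sided 5% alpha and 80% power, neither of which is in the document, and no target difference or SD is given to set against it.
- A reader might infer that outcomes were switched. Only one version of the record is at hand, so it cannot show this.

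**Conclusion.** The concern holds for the ranking of outcomes. None of the seven primaries measures what the titles and aim ask about, and both constructs in the aim are non-primary. The primary analysis as listed therefore cannot answer the trial's question, and the brief title claims more than the ranking supports. This rests only on the document's own text, with no assumed alpha, power, SD or success rule. Confidence is high for the mismatch. How it arose is unknown: it may be an error in completing the record or a deliberate choice, and only a dated earlier document could tell. It must be fixed because it determines what the trial may conclude.

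**What to change.** Amend the record and the report as follows.

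- Identify pain and anxiety as the outcomes that address the aim, with vital signs and laboratory values as supporting outcomes.
- Give the date of the re-ranking, state that it followed completion, and keep the listed ranking visible beside it.
- Report all seven listed primary outcomes whatever their results.
- Present pain and anxiety at both postoperative time points, without picking one after the fact.
- Describe the pain and anxiety results as non-confirmatory, unless a dated earlier document such as the ethics submission shows that they were primary. If one exists, cite it.
- Reword the brief title so that it names the question and does not assert a reduction.

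No new data are needed. The cost is that the vital signs lose primary status, the change has to be disclosed as made after completion, and the pain and anxiety claims become weaker than the brief title now states.

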## Eligibility

Minimum Age: 7 Years

Maximum Age: 12 Years

Sex: All

Gender Based: Yes

Accepts Healthy Volunteers: Yes

Criteria: Inclusion Criteria:

Child's criteria:

- Children aged between 7 and 12 years
- Ability to understand pain and anxiety scales
- Possession of communication skills
- Absence of mental issues
- Absence of physical illnesses
- Absence of chronic illnesses
- Willingness of the child and family to participate in the study
- No visual, hearing, or speech problems

Exclusion Criteria:

- Children younger than 7 years or older than 12 years
- Presence of any chronic illness that could affect pain and anxiety levels
- Presence of psychosocial issues
- Children or parents who meet the inclusion criteria but do not wish to wear the virtual reality headset (VRH) glasses
- Children who need to wear glasses other than the virtual reality headset (VRH)
- Children with hearing problems
- Children who do not wish to watch the shrek cartoon

## IPDSharing

Plan to Share IPD: No

